Cuparencu et al [35] recently reviewed validation criteria for BFIs and the general concepts of objective dietary assessment and listed known BFI candidates and their utility levels, as well as potential MBPs. The review also proposes research gaps. These include the identification of new MBPs and the discrimination of, for example, animal versus plant foods or healthful versus unhealthful foods. Additionally, more data on the interplay between BFI kinetics, frequency of food consumption, sampling schemes, sampling time windows, and different biospecimens are needed [35]. Furthermore, most studies still focus on biomarker discovery, often with untargeted analytical methods [33,36]. Beckmann et al [37] measured an MBP consisting of 54 BFI candidates in the urine samples of 15 participants who received a 3-day menu plan. The researchers were able to discriminate between the 3 dietary patterns that mimicked common UK diets [37]. Ultimately, more research is needed to unlock the full potential of BFIs and MBPs. Intervention studies specifically designed to measure BFIs in various samples from a diverse group of individuals consuming exact amounts and types of food, while considering dose- and time-response aspects, are necessary.

The JPI HDHL–funded project Plant*Intake* (acronym for “Combining biomarker panels and dietary intake data for improved assessment of healthful/unhealthful plant food intake”) aims to adapt the plant-based diet indices described by Satija et al [1] to better fit to European diets and common foods (European plant-based diet indices). Furthermore, an MBP reflecting the quantity and nutritional quality (healthful vs unhealthful) of plant foods in the diet will be derived using intake data and samples from previous studies. Validation of MBPs is paramount for future use. Therefore, the developed MBP will be validated with data from the intervention study PLAENTI (“Validating a multibiomarker panel for the assessment of quantity and quality of plant foods in the diet”), which is described in this study protocol.

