### Statistics

#### Outcomes

The primary outcome of the study is an MBP measured in urine and blood samples from participants in the arms LH, MH, and HH at defined time points during the 2-week intervention period. The analysis metric for the primary outcome is the change in levels of biomarkers contained in the MBP from visit 2 to visit 4, considered as a combined panel value. The variables will be aggregated and described by average values and SDs.

The secondary outcome is the MBP measured in urine and blood samples at defined time points in the two arms, HH and HU. The analysis metric for the secondary outcome is also the change in levels of biomarkers contained in the MBP from visit 2 to visit 4, considered as a combined panel value. The variables will be aggregated and described by average values and SDs.

Moreover, the comparability of the biomarker levels in the different types of urine samples (24-hour urine, spot urine, and pooled spot urine) will be investigated to gain insight into the applicability of spot urine sampling in epidemiological studies. Other outcomes of an exploratory nature will also be measured. Metabolomic analyses will be performed by measuring different classes of metabolites in the urine and blood samples. For microbiome parameters, the analysis metrics are alpha diversity (number and uniformity of species distribution within a microbiome), beta diversity (dissimilarity of the composition of different microbiomes), and abundance of individual taxa in different microbiomes. The results of the FFQ will be used to characterize the participants’ habitual diet.

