#### Statistical Methods

The aim of the primary statistical analysis is to detect a trend in the MBP as a function of the proportion of healthful plant foods consumed by the participants. Here, the values of the MBP determined at visit 4 are adjusted with the baseline values from visit 2. The MBP values are compared between the interventions using the Williams test. The comparison is made for the 3 diets with different proportions of healthful plant foods (low, medium, or high). For simplicity, it is assumed that the primary outcome is normally distributed and has a homogeneous variance. The statistical hypothesis is that the primary outcome will follow a trend for the ordered categories of low, medium, and high intake of healthful plant foods. Group HH, with a high proportion of healthful plant foods in the diet, serves as a control. The following 3 average values of the MBP are assumed for the 3 intervention groups: *μ*1*, μ*2*,* and *μ*3. All intervention groups have a comparable sample size. An average different response is expected in the group with low and medium consumption compared to the high consumption (control) of healthful plant foods. The global null hypothesis is formulated as *H*0*: μ*1*=μ*2*=μ*3 versus the alternative hypothesis *H*1*: μ*3*≥μ*2*≥μ*1, with at least one strict inequality. When modeling the MBP, adjustment is made for the following potential confounding variables: age, sex, body composition (assessed by BIA), and physical activity (assessed by accelerometry). The MBP is considered to be validated if a significant monotonic trend is observed (*P*<.05).

As the main secondary analysis, mean MBP values will be compared between the HH and HU intervention arms, characterized by similar proportions of plant foods but differing in nutritional quality (healthful vs unhealthful). Group differences will first be assessed using an independent-samples *t* test, followed by linear regression models incorporating the same set of adjusting variables.

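### One combined panel value serves both the plant-quantity outcome and the HH versus HU quality outcome, although those two arms have nearly equal plant share; a separate quality score is needed.

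*Protocol article*

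**What the plan says.** All references are to the protocol article.

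- **Objectives (end of the Introduction).** The primary objective is to estimate the quantity of plant foods from the panel (MBP). The secondary objective is to detect a difference in their nutritional quality.
- **Outcomes (Methods, Statistics).** For LH, MH and HH, the metric is how far the panel's biomarkers move between visits 2 and 4, with the panel "considered as a combined panel value". For HH and HU, the text reads: "The analysis metric for the secondary outcome is also the change in levels of biomarkers contained in the MBP". The interval is the same, and the result is again one combined value.
- **Statistical Methods.** The primary test is a Williams trend test over low, medium and high intake of healthful plant foods. For the secondary analysis, "mean MBP values will be compared between the HH and HU intervention arms, characterized by similar proportions of plant foods", first by t test and then by adjusted regression. No sub-score, quality score or multivariate comparison is named for HH versus HU.
- **Panel.** According to the Introduction, "an MBP reflecting the quantity and nutritional quality (healthful vs unhealthful) of plant foods in the diet will be derived". The Sample Size section says this happens later in the project. The biomarker list is in an appendix that is not shown.
- **Table 1.** Plant share of servings is 43% (LH), 62% (MH), 84% (HH) and 82% (HU).

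**The concern.** Quantity and quality are different constructs, and HH versus HU is the contrast designed to pull them apart: plant share is held roughly constant while quality changes. A single number that measures quantity well should barely move between these arms. A single number that moves clearly between them is not measuring quantity alone.

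The primary contrast does not resolve this. Across LH, MH and HH, the healthful share and the total plant share rise together, so a value that responds only to healthful foods would pass the trend test as easily as one that responds to all plant foods.

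At stake is how the results can be read. After a null HH-HU result, one could not tell a panel that carries no quality information from a summary that hid it. After a clear HH-HU difference, the claim that the same value estimates quantity would be in doubt.

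**Working it through.** **1. The plan's own power figure.** The article gives 0.81 for the three-arm Williams test (means 1, 2 and 3.8; variance 2.5; 15 per arm). Simulation of the Williams contrasts (42 df, any contrast significant) gives 0.813 if 2.5 is read as an SD, with two-sided 5% and LH as reference. With HH as reference it gives 0.845. Requiring all contrasts, one-sided, with HH as reference gives 0.822. With 2.5 read as a variance (SD 1.58), any-contrast power is at least 0.99. The figure covers only the primary trend; no power or effect size is given for HH versus HU.

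**2. If the value tracks total plant quantity.** Assume it is linear in plant share, with the stated HH-LH difference of 3.8 − 1 = 2.8 and SD 2.5. The expected HH-HU difference is 2.8 × (HH − HU share) / (HH − LH share). Power is for a t test with 15 per arm, 28 df and two-sided 5%.

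| Table 1 metric | HH − HU | HH − LH | Expected difference | In SD | Power |
|---|---|---|---|---|---|
| Servings | 84 − 82 = 2 | 84 − 43 = 41 | 0.14 | 0.05 | 0.05 |
| Calories | 87 − 85 = 2 | 87 − 50 = 37 | 0.15 | 0.06 | 0.05 |
| Weight | 86 − 79 = 7 | 86 − 47 = 39 | 0.50 | 0.20 | 0.08 |

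With SD 1.58 the powers are 0.06, 0.06 and 0.13. A pure quantity measure therefore leaves the quality test close to its false-positive rate, with no cancellation argument needed.

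**3. If the value separates HH from HU.** It then differs between diets two points apart in share of servings. A signed value (healthful up, unhealthful down) could satisfy both planned tests, LH < MH < HH and HU < HH, but it would no longer estimate total plant quantity.

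**4. Conditional risk of cancellation.** The effects here are assumptions. Take two independent sub-scores, each with SD 1: a healthful one higher in HH by d, and an unhealthful one higher in HU by r × d. Set d = 2.8 / 2.5 = 1.12, borrowed from the primary means with 2.5 as an SD.

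- Unsigned sum: standardised difference d(1 − r)/√2.
- Signed score (healthful minus unhealthful): d(1 + r)/√2.
- Noncentrality: standardised difference / √(2/15). Example for r = 0.5: 0.396 / 0.365 = 1.08 (sum) and 1.188 / 0.365 = 3.25 (signed).

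| Opposing movement r | Unsigned sum | Signed score |
|---|---|---|
| 0 | 0.55 | 0.55 |
| 0.25 | 0.35 | 0.74 |
| 0.5 | 0.18 | 0.88 |
| 0.75 | 0.08 | 0.96 |
| 1 | 0.05 | 0.99 |

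The healthful sub-score alone has power 0.84. At r = 0.5, moving d from 1.0 to 2.0 gives 0.16 to 0.46 for the unsigned sum and 0.80 to above 0.99 for the signed score.

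**The case against.** The best defence is that the panel does not yet exist. Its signs, weights and any sub-scores belong to the derivation work or to a full analysis plan, and a combined value need not be an unsigned sum. The trend hypothesis is framed on healthful plant foods, and the panel is meant to reflect both quantity and quality, so a value with healthful markers positive and unhealthful ones negative or absent would suit both planned tests. The marker list is not shown, so unhealthful-food markers may be few or missing. Markers shared between foods also make clean sub-scores hard to build.

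Much of this stands, and it rules out three stronger readings that a reader might infer:

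- *That the markers do cancel, leaving 5% power.* This needs same-sign aggregation and unhealthful-food markers in the panel. The article states neither, and 5% is only the exact-cancellation extreme.
- *That the quality objective cannot be answered.* This holds only if the value tracks total quantity.
- *That HU above HH would be declared a success.* The only validation criterion is the primary trend at P<.05. No success rule is attached to HH versus HU, and a two-sided test fits an objective of detecting a difference.

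The defence does not remove the central point. The article does state a metric, and it is the same one for both outcomes. A signed value rescues the quality test only by giving up total quantity, which is the primary objective. Later weighting decides which objective suffers.

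**Conclusion.** The concern holds in conditional form. One scalar is assigned to two constructs, and the two arms of the quality comparison differ by 2 points in servings and calories and by 7 in weight. If the scalar follows plant quantity linearly, the expected HH-HU difference is about 0.05 to 0.20 SD (SD 2.5), with power of 0.05 to 0.08. If it does not follow quantity, the primary trend cannot show that quantity is estimated. Only the sizes depend on the assumed linearity, means and SD; the dilemma does not depend on the panel weights.

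Cancellation is an additional possible loss of unknown size. Under the stated assumptions it ranges from nothing to the whole signal. This warrants a change to the metric. It does not mean that the comparison is certain to fail.

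**What to change.** Keep the combined value for quantity. Before any PLAENTI biomarker results are seen, specify a separate quality score as the HH-HU secondary metric:

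- healthful minus unhealthful markers, with weights fixed from the derivation studies;
- markers shared by both food classes left out, or weighted by the derivation data;
- the visit 4 value adjusted for visit 2, with HH above HU as the stated expected direction.

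Report the healthful and unhealthful sub-scores by arm, and report the combined-value comparison that the article now states alongside.

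No new participants, samples or assays are needed, because the same LC-MS data are used. The cost is one more score to specify and a documented change to the secondary outcome metric of a registered trial whose fieldwork is complete. If the derivation data cannot separate the two food classes cleanly, that limit should be stated with the score.

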#### Sample Size

The MBP to be validated in this study will be developed at a later stage of the Plant*Intake* project, so it was not possible to calculate the sample size prior to submission of the project proposal. As a Williams test is performed in the main statistical analysis, this was used as the basis for a sensitivity analysis. The calculation was performed using the R package “MCPAN” (R version 4.1.0, R Core Team). The option “Type: Williams” was used. Specifically, for a 3-arm design (for the primary outcome) with n=15 per arm and expected values for the MBP of 1 (LH), 2 (MH), and 3.8 (HH), and a homoscedastic variance of 2.5, a power of 0.81 was obtained [21,44-46]. A total of 60 participants were expected to complete the study, with even distribution between the groups.

Based on experience with previous studies, including a study with low, medium, and high intake of fruits and vegetables by Watzl et al [47] and the more recent JPI FoodBAll study (Universal Trial Number: U1111-1177-1536), a dropout rate of 12% was assumed. Therefore, in order to analyze a total of 60 participants, the goal was to enroll 68 participants in total.

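### The stated power of 0.81 does not follow from the stated inputs: with a variance of 2.5 the Williams test has power above 0.99, and 2.5 was probably the standard deviation

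*Protocol article*

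**What the plan says.** The Sample Size section explains that the multibiomarker panel (MBP) did not yet exist at planning, so no conventional sample size could be derived. It offers instead what it calls a sensitivity analysis based on the Williams test, run in the R package MCPAN: "The option “Type: Williams” was used". The design is given as "for a 3-arm design (for the primary outcome) with n=15 per arm", and the remaining inputs and the result as "expected values for the MBP of 1 (LH), 2 (MH), and 3.8 (HH), and a homoscedastic variance of 2.5, a power of 0.81". The section names no reference arm, significance level or sidedness for this calculation.

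The Statistical Methods section describes the primary test that the figure is meant to support. It says "Group HH, with a high proportion of healthful plant foods in the diet, serves as a control", states an ordered alternative in which the mean rises from LH through MH to HH, and sets the success rule: "The MBP is considered to be validated if a significant monotonic trend is observed", at P below .05.

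Table 2 (Study Population) shows 14, 15 and 15 completers in LH, MH and HH.

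**The concern.** The sentence prints a complete set of inputs and one output, so it can be checked. The LH to HH difference is 3.8 − 1 = 2.8. Against an SD of √2.5 = 1.58 that is 2.8/1.58 = 1.77 SD, which with 15 per arm is far too large an effect for a power of only 0.81. Against an SD of 2.5 it is 2.8/2.5 = 1.12 SD, which is about right for that power.

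This is the only power figure in the article, and it belongs to the test whose P value alone decides whether the panel counts as validated. The discussion also offers the protocol as a model for similar whole-supply studies. Someone who reused the printed variance would find 7 per arm sufficient (two-sided power 0.84 with LH as reference, 0.87 with HH). If the true SD were 2.5, 7 per arm would give only 0.46 to 0.50.

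**Working it through.** **Inputs.** From Sample Size: n = 15 per arm, three arms, means 1 / 2 / 3.8, variance 2.5. From Statistical Methods: 5% level, HH as control, ordered alternative. The reference arm and sidedness of the power calculation are not given, so every combination was tried.

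**Method.** With equal arms there are two Williams contrasts, in the order LH, MH, HH:
- LH as reference: (−1, 0, 1) and (−1, ½, ½)
- HH as reference: (−1, 0, 1) and (−½, −½, 1)

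For a contrast *c*, the noncentrality is Σcᵢμᵢ / (σ·√(Σcᵢ²/n)). The error degrees of freedom are 45 − 3 = 42, and the two statistics have correlation 0.866 under either reference. The 5% critical value from the joint t distribution is 1.862 one-sided and 2.194 two-sided. Power is the probability that at least one contrast exceeds it.

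**Step 1: the inputs as printed, σ = √2.5 = 1.581.**
- (−1, 0, 1): effect 2.8; standard error 1.581 × √(2/15) = 0.577; noncentrality 4.85
- (−1, ½, ½): effect (2 + 3.8)/2 − 1 = 1.9; standard error 1.581 × √(1.5/15) = 0.500; noncentrality 3.80
- (−½, −½, 1): effect 3.8 − (1 + 2)/2 = 2.3; standard error 0.500; noncentrality 4.60

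**Step 2: 2.5 read as the SD, σ = 2.5.** The standard errors become 0.913 and 0.791, and the noncentralities 3.07, 2.40 and 2.91.

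Power for at least one significant contrast at 5%, n = 15 per arm:

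| Reference, sidedness | Variance 2.5 | SD 2.5 (variance 6.25) |
|---|---|---|
| LH, two-sided | 0.995 | **0.814** |
| LH, one-sided | 0.998 | 0.890 |
| HH, two-sided | 0.997 | 0.845 |
| HH, one-sided | 0.999 | 0.912 |

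The printed 0.81 is not reproduced anywhere in the variance 2.5 column. In the SD 2.5 column it appears with LH as reference and a two-sided 5% level; a one-sided 2.5% level gives practically the same value.

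**Step 3: is the form of the test responsible?** At variance 2.5, the one-way ANOVA F test has power 0.993 and the single HH versus LH contrast 0.997 (two-sided). The choice of contrasts does not explain the gap.

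**Step 4: what SD would give 0.81?** For LH as reference, two-sided, the SD has to be about 2.515 (variance about 6.33). That is 2.5 to within rounding.

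**Step 5: achieved arm sizes.** With 14/15/15, SD 2.5 and 5%: LH as reference 0.80 two-sided and 0.88 one-sided; HH as reference 0.83 and 0.905.

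**The case against.** Three points can be made for the protocol.

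First, the SD explanation is not the only route to about 0.81. With SD 2.5, HH as reference, a one-sided 5% test and a requirement that both contrasts be significant, power is 0.82. If the variance is doubled to 5, as might be done for a change score, HH as reference with both contrasts significant two-sided also gives 0.82. Even the printed variance of 2.5 reaches 0.82 with LH as reference if both contrasts must be significant at a two-sided 1% level. This stands, and it means the cause cannot be settled from the article. It does not rescue the sentence: the article describes none of these settings, and the last conflicts with its own 5% criterion.

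Second, a reader might infer that the power was computed with LH as reference, and so for contrasts other than those to be analysed. The article does not support that as a fact. Sample Size names no reference arm; LH is obtained only by working back from 0.81, and one of the routes above uses HH. An article may also leave such software settings to the full protocol or analysis plan. At SD 2.5 the choice matters little two-sided (0.81 against 0.845).

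Third, a reader might infer that the trial is underpowered, or that its variance was understated 2.5-fold (6.25/2.5). Neither is shown. The second presumes that the label is wrong and the power right, when the reverse is possible. As to the first, the means and variance are provisional values for a panel not yet developed, follow-up is complete, and with 14/15/15 power remains 0.80 to 0.905 even at SD 2.5.

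**Conclusion.** The power sentence is wrong as written: at 5%, its inputs give 0.995 to 0.999, not 0.81. This rests on the usual definition of power for a multiple contrast test (at least one significant contrast), a pooled variance and the normality that the article itself assumes. It holds for either reference arm and either sidedness.

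That 2.5 is really the SD is the simplest explanation and matches to two decimals, but it remains an inference. If it is right with LH as reference and a two-sided level, the printed figure does not match the HH-controlled, ordered comparison in Statistical Methods, for which the power would be 0.845 two-sided or 0.912 one-sided. If instead the variance is truly 2.5, the power is understated.

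Neither reading calls the design, the primary test or the success criterion into question. It is a moderate reporting error, worth correcting because this is the trial's only planning figure.

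**What to change.** Look up the MCPAN call and correct whichever figure is wrong:
- If 2.5 was entered as the SD, restate the input as a common SD of 2.5 (variance 6.25).
- If the variance really is 2.5, restate the power as above 0.99.
- If another definition of power or another level was used, say so.

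In the same sentence, give the reference arm, level and sidedness of the calculation. Report the power for the contrasts and sidedness that Statistical Methods will use, at 15 per arm and at the achieved 14/15/15 (Step 5 gives the values for SD 2.5). State in Statistical Methods whether the P<.05 criterion is one- or two-sided, so that the two sections agree.

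The cost is one rerun of a short script and a corrected sentence or two. Enrolment, data and the primary analysis are unaffected.

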#### Statistical Methods

The aim of the primary statistical analysis is to detect a trend in the MBP as a function of the proportion of healthful plant foods consumed by the participants. Here, the values of the MBP determined at visit 4 are adjusted with the baseline values from visit 2. The MBP values are compared between the interventions using the Williams test. The comparison is made for the 3 diets with different proportions of healthful plant foods (low, medium, or high). For simplicity, it is assumed that the primary outcome is normally distributed and has a homogeneous variance. The statistical hypothesis is that the primary outcome will follow a trend for the ordered categories of low, medium, and high intake of healthful plant foods. Group HH, with a high proportion of healthful plant foods in the diet, serves as a control. The following 3 average values of the MBP are assumed for the 3 intervention groups: *μ*1*, μ*2*,* and *μ*3. All intervention groups have a comparable sample size. An average different response is expected in the group with low and medium consumption compared to the high consumption (control) of healthful plant foods. The global null hypothesis is formulated as *H*0*: μ*1*=μ*2*=μ*3 versus the alternative hypothesis *H*1*: μ*3*≥μ*2*≥μ*1, with at least one strict inequality. When modeling the MBP, adjustment is made for the following potential confounding variables: age, sex, body composition (assessed by BIA), and physical activity (assessed by accelerometry). The MBP is considered to be validated if a significant monotonic trend is observed (*P*<.05).

As the main secondary analysis, mean MBP values will be compared between the HH and HU intervention arms, characterized by similar proportions of plant foods but differing in nutritional quality (healthful vs unhealthful). Group differences will first be assessed using an independent-samples *t* test, followed by linear regression models incorporating the same set of adjusting variables.

As a further aim, biomarker levels will be compared between different urine samples (24-hour urine, single spot urine, and pooled spot urine). Temporal variability during the 2-week intervention will be characterized descriptively and by variance components. For this purpose, mixed-effects linear models with biomarker levels as the dependent variable, urine sample type and time as fixed effects, and participants as random effects will be applied. From these models, within- and between-participant variance and intraclass correlation coefficients will be estimated. Additional exploratory analyses can be conducted on metabolomic profiles, metabolic pathways, and further physiological or health-related variables. These outcomes will be analyzed using linear regression models. To account for multiple testing in high-dimensional metabolomics, *P* values will be adjusted using the Benjamini-Hochberg procedure.

In the case of missing data, the first step is to investigate what type of missing data occurs. If biomarker levels are below a reliable detection limit, these are modeled as “censored data.” A distinction will also be made as to whether the missing data are random or not, and they will be treated accordingly. We will not include the data of participants in subsequent analyses if an unacceptable adverse event occurred or if they were noncompliant.

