## Methods

### Study Design

The PLAENTI study was conducted at the Study Center for Human Nutrition of the Max Rubner-Institut, Federal Research Institute of Nutrition and Food in Karlsruhe, Germany, from January 9 to August 15, 2024. PLAENTI was designed as a randomized controlled trial with 4 arms. A parallel-group design was chosen to efficiently conduct the study and allow for direct comparison of results between the arms. A total of 66 participants were enrolled and randomized to 1 of 4 arms, stratified by sex. For logistic reasons, the study was conducted in 5 waves, each with a maximum of 16 participants. Each wave lasted a total of 4 weeks and started with a 1-week run-in period during which all participants consumed the same diet consisting of a low proportion of healthful plant foods to achieve comparable baseline levels of biomarkers. For the 2-week intervention period, participants were assigned to 1 of 4 interventions and received a diet that varied in the quantity and nutritional quality of plant foods to mimic different dietary patterns. The intervention was followed by a 1-week washout period, during which the participants returned to their habitual diet.

The study was carried out in an outpatient setting. Participants collected urine and stool samples and prepared and consumed food at home. Visits to the study center took place once a week on an identical schedule for all participants. Participants were asked to fast for at least 10 hours beforehand and underwent a series of standardized examinations and measurements described in detail below. Standard operating procedures were developed and tested for feasibility for all interviews, examinations, measurements, sample collections, sample preparations, and storage. Interviewers and examiners were extensively trained before and supervised during data collection. An overview of the study procedure is shown in Figure 1.

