### Study Design

A crossover design may be considered advantageous for validation studies due to the reduced interindividual variability [50]. On the downside, a crossover design would significantly increase the duration of a standardized diet, which may result in higher dropout rates and a reduced likelihood of good compliance [51]. Because of this, we chose a parallel-group design in PLAENTI, even though this might lead to differences in baseline biomarker levels or confounders between participants. However, the run-in period will have reduced these baseline variations. The 2-week intervention is expected to be sufficient to establish a stable biomarker pattern, as the sampling windows for BFIs with long elimination half-lives are approximately 6 days [35].

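### The panel analysis appears to use a visit 2 to visit 4 change score, the two statistics sections do not state this consistently, and visit 2 as a covariate would be at least as precise

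*Protocol article*

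**What the plan says.** Under Outcomes, the metric for the primary outcome (arms LH, MH and HH) is "the change in levels of biomarkers contained in the MBP from visit 2 to visit 4, considered as a combined panel value". The same metric is repeated there for the secondary comparison of HH with HU.

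Under Statistical Methods, the wording differs: "the values of the MBP determined at visit 4 are adjusted with the baseline values from visit 2". The panel values are then compared by the Williams test, with adjustment for age, sex, body composition and physical activity. The baseline panel value is not in that list. For HH versus HU, the section compares mean panel values by an independent-samples t test, followed by regression with the same adjusting variables. Baseline is not mentioned for that comparison.

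On the run-in, Study Design in the Methods says that "all participants consumed the same diet consisting of a low proportion of healthful plant foods to achieve comparable baseline levels of biomarkers". Study Design in the Discussion expects that "the run-in period will have reduced these baseline variations".

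**The concern.** The panel counts as validated if one trend test reaches P<.05, so the quantity entering that test should be fixed in one form. Outcomes gives a difference. Statistical Methods gives an adjustment that could be a difference or a regression on baseline. These are different estimators with different standard errors.

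If a plain difference is meant, it is the weaker choice. Subtracting visit 2 takes its full variation into the outcome, whether or not that variation predicts visit 4. A covariate uses only the predictive part. The run-in puts everyone on one diet before visit 2. That may remove stable dietary differences and so lower the correlation with visit 4, which would weaken the case for subtraction. With 14 or 15 completers per arm, precision matters.

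**Working it through.** **The plan's own figure.** The article gives no number for baseline handling. Its only related figure is the power of 0.81 under Sample Size, "for a 3-arm design (for the primary outcome) with n=15 per arm", with means 1, 2 and 3.8 and a variance of 2.5. A simulation of Williams contrasts (400,000 draws, 42 degrees of freedom, alpha 0.05) with variance 2.5 gives 0.995 to 0.999 for at least one significant contrast and 0.942 to 0.996 for all contrasts. The stated 0.81 is not reproduced. Reading 2.5 as an SD (variance 6.25) gives 0.815 two-sided with LH as reference (any contrast), or 0.822 one-sided with HH as reference (all contrasts). The article also does not say whether the variance is that of the change or of the visit 4 value. This is a separate matter, but it means that precision cannot be converted into power here without replacing a stated input.

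**Inputs that have to be assumed.**
- rho: within-arm correlation of the visit 2 and visit 4 panel values. Not given.
- k: SD at visit 2 divided by SD at visit 4. Not given.

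**Formulas**, in units of the visit 4 variance:
- change score: 1 + k² − 2·rho·k
- visit 2 as covariate: 1 − rho²
- difference: k² − 2·rho·k + rho² = (k − rho)², which is never negative

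**Results.**

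| k | rho | Change score | Covariate | Reduction |
|---|---|---|---|---|
| 1.0 | 0.2 | 1.60 | 0.96 | 40% |
| 1.0 | 0.5 | 1.00 | 0.75 | 25% |
| 1.0 | 0.8 | 0.40 | 0.36 | 10% |
| 0.7 | 0.2 | 1.21 | 0.96 | 21% |
| 0.7 | 0.5 | 0.79 | 0.75 | 5% |
| 0.5 | 0.2 | 1.05 | 0.96 | 9% |
| 0.5 | 0.5 | 0.75 | 0.75 | 0% |

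Example for k = 0.7, rho = 0.2: 1 + 0.49 − 0.28 = 1.21; 1 − 0.04 = 0.96; 1 − 0.96/1.21 = 21%.

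**When subtraction is worse than ignoring baseline.** The change score has more variance than visit 4 alone when k² − 2·rho·k > 0, that is, when rho < k/2. The threshold is 0.50 for k = 1, 0.35 for k = 0.7 and 0.25 for k = 0.5.

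**Cost of the covariate.** The primary comparison has 14 + 15 + 15 = 44 completers. With three arm means and, assuming one parameter each, four listed covariates, 44 − 3 − 4 = 37 residual degrees of freedom remain. Adding baseline leaves 36. Estimating its slope inflates the contrast variance by roughly 1/(37 − 2), about 3%. That can outweigh the gain only where rho is close to k.

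**The case against.** **Statistical Methods may already mean a covariate.** It deals with baseline in its own sentence, and the later list is headed as potential confounders, where a baseline outcome value need not appear. A reader might infer from the list that subtraction is certain; the text does not go that far. This stands. However, if a covariate is meant, the section departs from the metric fixed under Outcomes, so the two still have to be reconciled.

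**The size of the gain is not in the documents.** A reader might take 25% to 40% as the saving. That range needs k = 1 and rho between 0.2 and 0.5. The run-in argument cuts both ways: it may lower rho, but by shrinking baseline spread it also lowers k, which reduces the gain. The Introduction also notes that biomarker concentrations vary with age, sex, activity and body composition, which a week of common diet does not remove and which may keep rho up. All of this stands, so only a range can be given.

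**Unequal variance.** The plan says that "it is assumed that the primary outcome is normally distributed and has a homogeneous variance". A reader might infer from Tables 1 and 2 that the delivered doses refute this, since plant share times the SD of energy expenditure gives 0.50 × 510 = 255, 0.67 × 338 = 226 and 0.87 × 517 = 450 kcal in LH, MH and HH. These are spreads in plant calories of all kinds, not in panel values. They arise entirely from energy expenditure, which is calculated from fat-free mass and accelerometry, and the model already adjusts for body composition and activity. The documents do not show unequal panel variance.

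**Model detail belongs in the analysis plan.** This would be fair if the article were silent. It is not: it fixes one metric and then describes the adjustment in other terms.

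**Conclusion.** The point holds as one of precision and consistent specification. The stated metric is a change score for both comparisons, and nothing in Statistical Methods clearly provides a baseline covariate. No bias follows, because the change score is valid under randomisation.

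The direction of the gain from a covariate is fixed by (k − rho)², apart from about 3% for the extra parameter. Its size is not known: over the assumed values shown, it runs from 0% (k = 0.5, rho = 0.5) to 40% (k = 1, rho = 0.2). No loss of power can be stated, because the variance in the sample size section is not tied to either the change or the visit 4 value and does not reproduce the stated power. The change is worth making because the visit 2 data already exist and the cost is close to nil.

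**What to change.** State in both Outcomes and Statistical Methods that the primary analysis is an analysis of covariance: visit 4 panel value on arm, with the visit 2 panel value and the listed variables as covariates, and Williams-type contrasts of the adjusted means. The visit 2 to visit 4 change can stay as a descriptive summary. If the change is kept as the dependent variable with visit 2 as a covariate, the arm contrasts are identical.

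Use the same baseline-adjusted model as the main HH versus HU comparison, in place of the unadjusted t test. A version robust to unequal variance can be added, at most as a sensitivity analysis.

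The cost is a change of wording and one degree of freedom per model. No new samples or measurements are needed. The article describes the biomarker analysis as still to be done, so the choice can be recorded before panel values are seen.
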